#### Face-to-face intervention element

Building on the Kenyan Shamiri intervention [11], the face-to-face element of maisha involves four group sessions grounded in the wise interventions framework [44]: growth mindset (sessions 1 and 2), gratitude (session 3), and value affirmation (session 4). The sessions will run weekly for 1 h over four weeks, delivered in small groups of 6 to 7 young people by lay providers (aged 18 to 22). Supervision (ratio of 1:5) will be provided by trained clinical psychologists (see Supplementary methods 2).

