##### Process evaluation

A mixed-methods process evaluation will be conducted using the framework developed by Grant et al. [58]. The process evaluation aims to understand the trial delivery, implementation context, and participant engagement. We will use purposive sampling to select participants from each intervention arm and across study sites to ensure that all subgroups are represented.

Under trial delivery, we will assess the reach, fidelity, dose, and adherence to the intervention. Reach will be measured using the proportion of eligible participants, the proportion that consented, drop-outs, and representativeness by demographic characteristics. Fidelity, dose of, and adherence to the face-to-face element will be assessed using a self-report questionnaire, attendance sheets, observation, and audio ratings of selected sessions, and in-depth interviews with lay providers (*n* = 10) and supervisors (*n* = 3). Fidelity, dose of, and adherence to the digital element will be assessed using error reports, app log files (e.g., number and duration of completed EMA and EMI enhancing, consolidating, and interactive exercises). Where feasible, participants who discontinue the intervention will also be invited to provide feedback.

For the implementation context, we will qualitatively assess the need for adaptation, barriers, enablers, and contextual factors (structural, environmental, and cultural) that may influence implementation and outcomes. For engagement, participants will fill in a feedback questionnaire about their experiences post-intervention. In-depth interviews (IDIs) and focus group discussions (FGDs) will be conducted with a purposive sample of young people (*n* = 20) from the three intervention arms.

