### Data processing and analysis

#### Quantitative data

A detailed statistical analysis plan will be published before conducting any analyses. Data will be accessed only after completion of the final post-intervention data collection. Data will be analyzed according to the intention-to-treat principle. Data processing will involve cleaning, (re-) coding, and formatting of variables for statistical analysis. The sample size was calculated using the Shiny CRT Calculator [69]. Using a parallel design with baseline measure and assuming an average intra-cluster correlation (ICC) of 0.05 [70], and α = 0.05, 25 clusters per arm with 6 participants each (600 participants) will yield 80% power (β = 0.8) to detect a mean difference of ≥ 0.36 between the blended intervention and the control condition (CAU). The assumed minimal mean difference aligns with effects observed in previous RCTs evaluating the individual intervention elements [27, 30]. Considering a 10% dropout rate, 666 young people will need to be recruited.

The primary analysis will apply a mixed-effects linear regression model to examine the effect of the blended intervention compared to the control condition (CAU) on emotion regulation difficulties. The level of ER difficulties will be compared between the experimental and the control conditions at post-intervention. ER difficulties (DERS-SF) at post-intervention will be entered as the dependent variable, and ER difficulties at baseline, condition (= allocation), and setting (= location or context in which participants receive the intervention) will be entered as independent variables. While random allocation to intervention arms is designed to balance baseline characteristics, we will verify balance post-randomization and – if imbalance is identified – incorporate appropriate covariate adjustments to improve precision and validity of effect estimates. To account for clustering, the model will include a random intercept for the allocation unit (i.e., face-to-face group), with individual (level 1) nested within these units (level 2), reflecting the two-level structure. The model will be fitted using Restricted Maximum Likelihood (REML), and the main effect of condition will be estimated using a Wald-type test (α = 0.05). Potential regression to the mean will be considered in the interpretation of results.

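### The primary model has no lay-provider term, so the A versus D standard error is too small if arm A providers lead groups in more than one modelled unit

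*Protocol article*

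**What the plan says.** All references are to the protocol article.

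- **Random effects (Quantitative data).** There is one random effect: "the model will include a random intercept for the allocation unit (i.e., face-to-face group". The hierarchy is "with individual (level 1) nested within these units (level 2), reflecting the two-level structure".
- **Fixed effects and test (same section).** Baseline DERS-SF, condition and setting are the covariates. For inference, "the main effect of condition will be estimated using a Wald-type test (α = 0.05"; the reference distribution is not named. Secondary outcomes follow the same modelling approach.
- **Sample size (same section).** It rests on a single clustering parameter, "assuming an average intra-cluster correlation (ICC) of 0.05", and states that "25 clusters per arm with 6 participants each (600 participants) will yield 80% power".
- **Delivery (Face-to-face intervention element).** Sessions are "delivered in small groups of 6 to 7 young people by lay providers (aged 18 to 22", with supervision at 1:5. Under Blended intervention, the session leaders also help arm A participants with the app by chat.
- **Staff counts (Process evaluation).** The only numbers given are for "in-depth interviews with lay providers (*n* = 10) and supervisors (*n* = 3". The article does not say how many providers there are or how many groups each leads.
- **Allocation units (Randomization and blinding).** These are natural sub-groups such as class levels, and whole community organisations.

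**The concern.** A lay provider can affect the outcomes of everyone he or she leads. This source of correlation exists in arms A and C and not in arm D. If one provider leads one modelled unit, the unit's random intercept absorbs the provider effect and nothing is lost. If one provider leads several, those units share a component that the two-level model treats as independent between units. The arm A mean is then less precise than the model reports. What is at stake is the single confirmatory comparison, A versus D: its interval would be too narrow and its test would reject too often. The secondary-outcome comparisons of A with D use the same model and would have the same too-narrow intervals.

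The point concerns a possible level above the modelled unit. Which unit carries the existing intercept is a separate question, although the size of the harm depends on the answer.

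**Working it through.** **1. The plan's own figure.** Inputs: 25 clusters of 6 per arm, ICC 0.05, difference 0.36. The article gives no SD, so SD = 1 is assumed, with a two-sided 5% test.
- Design effect = 1 + (6 − 1) × 0.05 = 1.25; effective n per arm = 150 / 1.25 = 120.
- SE = √(2 × 1.25 / 150) = 0.1291; 0.36 / 0.1291 − 1.96 = 0.83, so power is 79.6%.

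The stated 80% reproduces with no provider component.

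**2. Is more than one group per provider plausible?**
- Groups needed in arms A and C together: 2 × 150 / 7 ≈ 43 up to 2 × 166.5 / 6 ≈ 56.
- One provider per group at 1:5 supervision needs about 43 / 5 to 56 / 5, or roughly 9 to 11 supervisors.
- If the 3 interviewed supervisors were the whole team, there would be about 15 providers, and 50 / 15 ≈ 3.3 groups each. This is an inference and is not stated.

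**3. Size for A versus D.** Assumptions: each group is its own modelled unit; group ICC is 0.05; provider ICC ρ is added in arm A only; residual variance is 0.95; post-intervention outcome only, without covariates. Let S be the sum of squared groups per provider, divided by 25².
- 25 providers: S = 25 / 625 = 0.04.
- 13 providers (twelve lead two groups, one leads one): S = 49 / 625 = 0.0784.
- 8 providers (seven lead three groups, one leads four): S = 79 / 625 = 0.1264.

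True variance of the arm A mean: V_A = ρS + 0.05/25 + 0.95/150.

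Variance the two-level model expects for it: E_A = (ρ + 0.05 + 0.95/6 − V_A) / 24.

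Arm D variance, correct under the model: V_D = 0.05/25 + 0.95/150 = 0.008333.

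True SE / model SE = √[(V_A + V_D) / (E_A + V_D)].

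Example, 8 providers and ρ = 0.05: V_A = 0.00632 + 0.008333 = 0.014653; E_A = (0.258333 − 0.014653) / 24 = 0.010153; ratio = √(0.022987 / 0.018487) = 1.115.

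Approximate type I error = 2 × P(T48 > 2.011 / ratio).

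| Arm A providers | SE ratio, ρ = 0.01 / 0.02 / 0.05 | Type I error, t(48) |
|---|---|---|
| 25 | 1.00 / 1.00 / 1.00 | 5.0% |
| 13 | 1.012 / 1.023 / 1.052 | 5.3 / 5.5 / 6.2% |
| 8 | 1.026 / 1.050 / 1.115 | 5.6 / 6.2 / 7.8% |

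Simulation of cluster means agrees to within simulation error: about 5.2–6.2% with 13 providers and 5.5–7.7% with 8.

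**4. Separating out the reference distribution.** With no provider effect, a normal critical value on 48 df gives 2 × P(T48 > 1.96) = 5.6%. That excess over 5% is not due to providers, which is why the table uses t(48).

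**5. A versus C.** If the same providers lead groups in both arms in balance, with a common effect, the provider component cancels in the difference. The true SE is then about 0.90–0.98 of the model SE for ρ = 0.05 down to 0.01, so the two-level interval is too wide.

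**The case against.** **The trigger is not in the document.** Nothing says that a provider leads more than one group. A reader might take the 10 providers and 3 supervisors as the whole workforce and infer about five groups per provider. The article does not support this. They are interview numbers, qualitative collection follows information power, and as a workforce they do not match the 1:5 ratio (3 supervisors would imply 15 providers). Delivery detail is referred to a supplement that is not at hand. This objection stands, so the point must remain conditional.

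**An allocation-unit intercept may already cover it.** Where one class level or community organisation holds several groups and a provider works only there, the unit's intercept absorbs the provider effect. This also stands. The harm arises only when a provider spans modelled units.

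**The size is assumed and modest.** No provider ICC is given, and the top of each range sets it equal to all the clustering the sample size allows for. If about 15 providers worked evenly across A and C, the inflation would be at or below the 13-provider case. This is correct.

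**It belongs in the analysis plan.** This is only partly right. A detailed plan is promised, but the article itself states the structure and calls it two-level, so the gap is in a stated rule.

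**The setting covariate handles it.** It does not in general. The provider effect exists in A and not in D, so a main effect of setting does not remove it.

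**Conclusion.** The point holds in conditional form. The primary model is fixed at two levels without a provider term. If arm A providers lead groups in more than one modelled unit, and provider variance is above zero, the A versus D standard error is too small. For provider ICC 0.01–0.05 the true SE is about 1–5% above the model's with 13 arm A providers (type I error about 5.2–6.2%) and about 3–12% above with 8 (about 5.5–7.7%). The provider counts and ICCs are assumptions. With one modelled unit per provider there is no harm.

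Three stronger readings are not supported:
- **That the stated power is wrong.** It reproduces on its own inputs.
- **That every contrast involving C rejects too often.** These contrasts are exploratory and are read from effect sizes and intervals. C versus D and C versus B could have too-narrow intervals, while A versus C can err the other way if providers are shared.
- **That all of the excess under a normal Wald reference comes from providers.** About 5.6% arises with no provider effect.

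This is a worthwhile, inexpensive improvement, not a demonstrated error in the primary result.

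**What to change.** Record a provider ID for each face-to-face group alongside the attendance sheets already planned, and state the number of providers and the groups each one leads. Add to Quantitative data, and carry into the analysis plan:

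*Where a lay provider leads groups in more than one modelled unit, a provider random intercept, active only in the face-to-face arms (A and C), is added to the cluster intercept, and condition effects are tested with Satterthwaite or Kenward–Roger degrees of freedom. Otherwise the provider term is omitted.*

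The cost is one ID field and one conditional variance term. The interval may be slightly wider. With few providers the variance may be estimated at zero, in which case the standard error returns to its two-level value, so the estimate should be reported. The ID should be logged during delivery, because the link between provider and group may be hard to recover afterwards.

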### Goals and hypotheses

This study has three specific goals:

Test the efficacy of the blended intervention, MAISHA, on ER difficulties (primary outcome) among young people in Kenya. We hypothesize that participants allocated to the blended intervention condition (digital + face-to-face) will exhibit lower levels of ER difficulties compared to those in the control condition (CAU) at the post-intervention stage.Examine the signals of efficacy of the blended intervention on secondary mental health outcomes. We hypothesize that participants assigned to the blended intervention will show higher positive affect, more adaptive emotion beliefs, and greater use of adaptive ER strategies, as well as lower negative affect, emotional reactivity, and symptoms of depression, anxiety, and stress compared to CAU. We will also compare the three intervention conditions with each other to explore the potential contribution of intervention elements to the overall effects.Assess the acceptability, desirability, usability, and safety of the blended mental health intervention components. We postulate that the blended intervention will be culturally acceptable, desirable, usable, and safe for participants.Investigate proximal signals of efficacy of momentary intervention components of the digital element. We hypothesize that these intervention components will lead to short-term improvements in momentary negative affect and ER difficulties. Using a micro-randomized trial nested within study arms that include the digital element, we will also explore when, under what conditions, and for whom specific components are effective.

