## Study methods

### Study design and setting

This protocol was developed following the SPIRIT 2025 Statement [35] (see Additional File 1: Supplementary methods 5) and will be reported in line with CONSORT 2025 guidelines [36]. In a 2 × 2 parallel group, cluster-randomized controlled factorial trial design, young people aged 13–25 with difficulties in ER will be randomly assigned at a ratio of 1:1:1:1 to one of four conditions: (A) the full blended MAISHA intervention, combining the digital with the face-to-face element; (B) the digital app only; (C) the face-to-face element only; or (D) broadly defined care as usual (CAU). Participants will be recruited from high schools, universities, and community-based organizations for out-of-school individuals. Randomization will be conducted off-site using a computer-generated sequence, and outcome assessment and statistical analyses will be blinded. The primary comparison will assess the superiority of the full blended intervention (A) over CAU (D) in reducing ER difficulties. Exploratory comparisons between all intervention conditions will also be conducted to inform future implementation.

Nested within the cluster RCT, we will conduct a micro-randomized trial [37] to determine the proximal effects of digital intervention components and what factors might influence those effects. Using repeated, within-participant randomization to all digital components of the MAISHA intervention, each participant in study arm A (digital and face-to-face elements) and B (digital only) will be randomized to digital intervention components (i.e., breathing, imagery, diary techniques, or control) at multiple time points (decision points) throughout the study. Decision points will be triggered in moments of high negative affect or stress, indicated by a participant’s EMA response crossing a pre-defined threshold (see Fig. 1).

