#### Randomization and blinding

After screening and baseline data collection, participants will be randomized at the cluster level to one of the four study arms using permuted block randomization with blocks of four clusters each. To minimize the risk of cross-contamination within schools and small community-based organizations, naturally occurring sub-groups (e.g., class levels in schools) will be treated as allocation units and assigned to the same intervention arm. In case of community-based organizations, which are community-led groups based on shared interests (e.g., sports initiatives) [66], participants from a given CBO will be randomized to the same intervention condition. The randomization procedure will be carried out centrally and off-site using a computer-generated allocation sequence. Participant personal identification data will be stored separately from the process and outcome data. Assessors will be blind to the allocation of participants, data specific to the experimental groups will be stored separately and breaks in masking will be documented. Unblinding of assessors will only occur in exceptional cases where knowledge of the allocation is necessary for participant safety.

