Secondary measures - including positive and negative affect, symptoms of depression, anxiety, and stress, emotional reactivity, emotion beliefs, ER strategies, and interpersonal ER - will be analyzed using mixed-effects linear regression models, consistent with the approach described for the primary analysis. Exploratory analyses comparing the other intervention conditions (e.g., face-to-face and digital only against CAU) will be conducted to explore the potential contribution of intervention elements to overall effects and generate hypotheses for future implementation.

Exploratory analyses will include subgroup analysis to examine whether signals of efficacy of the blended intervention differ across specific groups. These analyses will be conducted within the primary mixed-effects model using interaction terms. We will examine proximal signals of efficacy of digital intervention components using data from the micro-randomized trial. Mixed-effects linear regression models with EMA observations (level 1) nested within individuals (level 2) will be applied to account for the hierarchical structure of longitudinal EMA data. Variables will include momentary negative affect, stress, and momentary ER. EMA data before and after momentary intervention components will be compared and types of EMI exercises (i.e., breathing, imagery, diary, control) will be included as independent variables. Results from all exploratory analyses will be interpreted using effect sizes and 95% confidence intervals rather than formal significance testing. Data from the process evaluation, acceptability, desirability, usability, and safety, sample characteristics, and baseline measures will be summarized descriptively.

We assume data will be Missing at Random (MAR) and will explore missingness patterns to assess this assumption. Continuous variables will be presented using means and standard deviations or medians and interquartile ranges; categorical variables using frequencies and percentages. All statistical analyses will be conducted in R.

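### The EMA model for the micro-randomised trial leaves out the randomised allocation unit, so some exploratory confidence intervals will be somewhat too narrow if exercise effects differ between units

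*Protocol article*

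**What the plan says.** The Study design and setting section places the micro-randomised trial inside the cluster trial: "Nested within the cluster RCT, we will conduct a micro-randomized trial". It covers both arms that contain the app: "each participant in study arm A (digital and face-to-face elements) and B (digital only) will be randomized to digital intervention components". Under Randomization and blinding, arms are assigned to groups of people: "participants will be randomized at the cluster level to one of the four study arms using permuted block randomization". The units are natural sub-groups such as class levels, or whole community organisations.

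The Quantitative data section gives two different hierarchies. For the primary outcome, "the model will include a random intercept for the allocation unit (i.e., face-to-face group", "with individual (level 1) nested within these units (level 2". For the momentary data, "Mixed-effects linear regression models with EMA observations (level 1) nested within individuals (level 2) will be applied", with exercise type as an independent variable and no term for the allocation unit.

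On the aim of this part, Goals and hypotheses says that "we will also explore when, under what conditions, and for whom specific components are effective". The moderators are not listed. Exploratory results are to be read from effect sizes and 95% confidence intervals instead of formal tests.

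**The concern.** The same people are treated as clustered in the primary model and as independent of one another in the momentary model. Within-person randomisation removes part of the problem, because a person's exercise and control moments share the same class or organisation, so a shared level drops out of the contrast. It does not remove a shared response to the exercises. The article gives a reason to expect one: arm A participants attend small-group sessions together, and the lay provider leading a group also helps with problems in the app through a built-in chat.

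If exercise effects do differ between units, the information about the average effect, or about a moderator fixed at unit level, grows with the number of units as well as with the number of people. A model that counts roughly 300 independent people (2 arms × 25 clusters × 6) then gives intervals that are too short. Because interval width is the declared basis for interpretation, this would overstate certainty about whether the exercises work on average and which settings or groups benefit.

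**Working it through.** **The plan's own figure.** Inputs from the Quantitative data section: 25 clusters per arm, 6 people each, difference 0.36, and "assuming an average intra-cluster correlation (ICC) of 0.05". Assumed: standard deviation 1 and a two-sided test.

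- Design effect = 1 + (6 − 1) × 0.05 = 1.25.
- Effective size per arm = 150 / 1.25 = 120.
- Standard error = √(2/120) = 0.129, and 0.36 / 0.129 = 2.79. Power = Φ(2.79 − 1.96) ≈ 79.6%, against 80% stated.
- Recruitment = 600 / 0.9 = 666.7, against 666 stated.

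The plan's figures reproduce with the cluster level included. There is no corresponding figure for the micro-randomised trial.

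**Contrasts in momentary level.** If arms A and B were compared on momentary level with clusters ignored, the standard error would be too small by √1.25 = 1.118 at the stated correlation of 0.05, with coverage of about 92%. That correlation refers to levels of the trial outcome and does not carry over to the exercise effect.

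**Contrasts in the exercise effect.** Each person contributes an exercise-minus-control difference. Let τ² be the variance of true exercise effects between people, ρ the share of τ² lying between units (the slope ICC), and v the sampling variance of one person's difference. Then

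- effective correlation of the differences = ρτ² / (τ² + v),
- SE ratio = √(1 + (6 − 1) × effective correlation).

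Assumptions, none of them in the article: τ = 0.3 residual SDs, and 20 or 60 observations per person split equally between exercise and control. Then τ² = 0.09, and v = 2/10 = 0.200 or 2/30 = 0.067.

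Example with ρ = 0.05 and 20 observations: 0.05 × 0.09 / 0.29 = 0.0155, and √(1 + 5 × 0.0155) = 1.04.

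A simulation (6,000 replicates; two arms, each with 25 clusters of 6; clusters ignored in the analysis) gives the following for A-versus-B modification of the exercise effect. Each pair is 20 / 60 observations.

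| Slope ICC | SE ratio, formula | SE ratio, simulated | Coverage of nominal 95% interval |
|---|---|---|---|
| 0 | 1.00 / 1.00 | 1.00 / 1.00 | 95.2% / 94.9% |
| 0.05 | 1.04 / 1.07 | 1.04 / 1.07 | 93.9% / 93.4% |
| 0.10 | 1.07 / 1.13 | 1.08 / 1.14 | 93.3% / 91.3% |
| 0.20 | 1.14 / 1.25 | 1.15 / 1.24–1.26 | 91.5–91.7% / 88.1–89.1% |

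The average proximal effect behaves in the same way: simulated SE ratios are 1.04 / 1.06 at 0.05, 1.08 / 1.15 at 0.10 and 1.14–1.15 / 1.25 at 0.20.

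For a person-level moderator balanced within each cluster, the SE ratio is 0.95 to 1.01 and coverage 95% to 96% throughout. There is no narrowing.

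**A second set of assumptions.** Take τ = 0.4, 15 or 30 decision points with 75% exercise and 25% control, and a slope ICC of 0.05. Then v = 1/(0.75T) + 1/(0.25T) = 0.356 or 0.178, the effective correlation is 0.008/0.516 = 0.0155 or 0.008/0.338 = 0.0237, and the SE ratio is 1.04 or 1.06. Coverage is 94.1% or 93.6%.

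**The case against.** The strongest reply is that this is an exploratory analysis, that a detailed statistical analysis plan is promised before any analysis, and that the sentence on the EMA model only explains how repeated measurements are handled. Random-effects detail is commonly left to that plan. This limits the weight of the point but does not remove it: the article names the levels of the model and stops one short of the structure it uses for the same participants a paragraph earlier. A plan that follows the text would carry the omission forward.

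The reply is right on four further matters, where a reader might infer more than the article supports.

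- A reader might conclude that all intervals on who benefits are too narrow. They are not. Only moderators that follow the unit, wholly or in part, are exposed. Questions about when and under what momentary conditions vary within the person.
- A reader might take A versus B to be a planned moderator here. The article never says so. It is a natural comparison, but only an inference.
- A reader might apply the stated correlation of 0.05 to the exercise effect. It belongs to the trial outcome, and a slope ICC of 0 is possible. In that case there is no defect.
- A reader might expect much larger error rates. These arise mainly if the model also lacks a person-level slope for exercise. Under the second set of assumptions, dropping that slope alone, with no variation between clusters, gives false-positive rates of 10.4% and 15.5% for a nominal 5% test. That is a separate matter from the missing cluster level, and the article does not say whether such a slope is included.

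**Conclusion.** The point holds in a limited form and is minor. The EMA model as stated omits the randomised unit that the primary model includes. If exercise effects vary between units, intervals are somewhat too narrow for the average proximal effect and for moderators that follow the unit: setting, class level, personal characteristics such as age or education level so far as they track these, and arm A versus B if it is examined.

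With 25 clusters of 6 per arm and assumed slope ICCs of 0.05 to 0.20, the standard error for an A-versus-B modification is too small by a factor of about 1.04 to 1.26, with coverage from about 94% down to 88%. At the lower end the effect is hardly noticeable, and at a slope ICC of 0 it vanishes. These sizes rest on assumed values for the spread of exercise effects and the number of observations per person. The primary comparison of the blended intervention with care as usual is not touched.

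**What to change.** Keep the individual level and add one line to the analysis plan: either standard errors for the EMA models are clustered on the allocation unit, or a random effect for that unit is added, with a unit-level slope for exercise versus control where it can be estimated. The unit should be the one actually randomised (class level or organisation), since arm B has no face-to-face group. The same line can say whether a person-level slope for exercise is included, and which moderators, if any, are fixed at unit level.

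The cost is slightly wider intervals for the average proximal effect and for unit-level moderators. No new data are needed, and sample size and primary analysis stay as they are.
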